# **Study endpoint**

# There is a statistically/clinically significant reduction in the study parameters between the subjects randomized to the Anti-aging applicator with prototype cream and the subjects randomized to manual application of the prototype cream.

# **Adverse Events**

Subjects will be examined at each study visit to determine if they experienced any adverse events. Any adverse events will be reported and an assessment will be made of the relationship of the reaction to the study product by the Principal Investigator and recorded as “probably related”, “possibly related”, “unrelated”, or “unknown”.

Adverse events related to the study will be documented at each study visit and will be recorded and handled according to the regulations.

**Study records**

Study records including study related documents pertaining to the conduct of the study will be kept in a secure area. Patient information will remain confidential.

**Safety**

All products used in this study will be reviewed for safety and biocompatibility as per standard operation procedures.

**Statistical Analysis**

The clinical grading scores and tolerance scores (subjective and objective) will be compared for both treatments and with their respective baselines: Anti-aging applicator + prototype cream and manual application of prototype cream at all the time points (week 4 and week 8).

For comparison with baseline of each treatment, the normality of the difference (from baseline) will be tested with Shapiro-Wilk test. The following statistical analyses will be performed for comparisons:

- Parametric Paired t-test in case of normality of differences
- Non-parametric Wilcoxon Signed Ranks test in the inverse case

For comparing both the treatments with each other, the normality of the difference (between treatments) will be tested with Shapiro-Wilk test. The following statistical analyses will be performed for comparisons:

- Parametric t-test in case of normality of differences
- Non-parametric Mann-Whitney test in the inverse case

For normality tests, the statistical significance level is set at p≤0.01. For all other statistical tests, the statistical significance level is set at p≤0.05.

Clinical significance is equal to or greater than a half point difference in clinical grading scores. Clinical significance will be addressed only when the data is statistically significant.

The self-assessment data will be analyzed by a consumer perception team.

Final Report

Following the completion of the study, a final report will be prepared. The report will detail the number of subjects who completed the study, any protocol deviations, adverse events, modifications, and a summary of the data.

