**Study Endpoints**

*Efficacy Endpoints*

- Clinical grading at baseline, week 4, and week 8:
  - Face: Forehead wrinkles, cheek wrinkles, lip area wrinkles, global facial wrinkles, facial sagging, glabella lines, texture
  - Neck: Overall appearance, sagging, neck folds, texture
- Digital imaging procedures: Vectra 3D Imaging System, Canfield
- Subject completed self-assessment questionnaires (week 4 and week 8).

*Safety/Tolerability Endpoints*

- Clinical grading of objective irritation parameters and subject reporting of subjective assessment parameters at baseline, week 4, and week 8.
- Monitoring of adverse events throughout the course of the study.

Overview

| **Study Title** | Evaluating the efficacy of a prototype massage applicator using a prototype cream and manual application of a prototype cream on a population with signs associated with aging skin |
| --- | --- |
| **Sample Size** | 45 enrolled to complete 42 |
| **Study Design** | - 2 arms:   - tagged prototype massage applicator using a sonic handle and prototype cream   - Manual application of prototype cream - Subjects randomized to a treatment application method (prototype massage applicator + prototype cream, manual application of prototype cream) - Home use: two times per day; 7 days per week   - Prototype massage applicator using prototype cream for 2 minutes and 15 seconds (30 seconds forehead, 1 minute mouth and cheek area, and 45seconds jawline and neck)   - Manual application of facial cream (using their normal technique for applying facial creams) - Duration: 8 weeks - Study visits: Baseline, 4 and 8 weeks - Clinical assessments: Baseline, 4 and 8 weeks - Self-assessment questionnaires: 4 and 8 weeks   A sunscreen (SPF 30) will be given to subjects at the baseline visit for daily use (mornings only) and to be reapplied during the day as needed for the duration of the study |
| **Number of Arms** | 2 arms:   - Prototype massage applicator using a sonic handle and prototype cream - Manual application of prototype cream |
| **Test Sites** | - Face - Neck |
| **Key entrance criteria** | - Available for 3 study visits - Between the ages of 65-75 years - Have not participated in a study evaluating Anti-aging applicators/devices - Fitzpatrick skin types I, II, III - Non-smokers - Fine lines/wrinkles: global facial wrinkles ( ≥ 4 on a 10 pt. scale) - Sagging facial skin ( ≥4 on a 10 pt. scale) |

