***D=dispense; R= Return**

**** only if additional product is needed**

C. Assessments:

*Clinical grading assessments:*

Clinical grading of efficacy parameters will be performed at baseline, 4 & 8 weeks. Subjects will be provided with a black headband to keep hair away from the face and instructed on proper headband placement. Full face and neck efficacy parameters will be assessed on each subject using the modified Griffiths’ 10-point scale recording to the following numerical definitions (half-point scores may be used as necessary to more accurately describe the skin condition):

0 = none (best possible condition)

1 to 3 = mild

4 to 6 = moderate

7 to 9 = severe (worst possible condition)

The following parameters to assess the **face** will be evaluated using the indicated scale anchors:

| Parameter | Location | 0 = | 9 = |
| --- | --- | --- | --- |
| Facial sagging (global) | Overall | None | Severe sagging |
| Texture | Overall | Even | Severely rough and uneven skin |
| Fine lines/wrinkles  Glabella lines | Forehead, cheek, lip, global face  Forehead | None    None | Numerous, deep wrinkles  Numerous, deep lines |

The following parameters to assess the **neck** will be evaluated using the indicated scale anchors:

| Parameter | Location | 0 = | 9 = |
| --- | --- | --- | --- |
| Sagging (global) | Overall | None | Severe sagging |
| Neck folds  Texture  Overall appearance | Overall  Overall  Overall | None    Even  Very healthy | Numerous, deep folds  Severely rough and uneven skin  Very unhealthy |

*Tolerance assessments:*

Tolerability evaluations will be performed at baseline, weeks 4 and 8. Local cutaneous tolerability will be evaluated by assessing the overall signs and symptoms of erythema, edema, dryness, and peeling and by the subject reporting the overall degree of burning, stinging, itching, and tingling.

For overall assessments of subjective irritation, subjects will report the degree of any parameters that they typically experience when using a product similar to the test material(s) at the baseline visit. At post-baseline time points, subjects will report the degree of any of these symptoms they have experienced since the previous time point.

The following static (without reference to any prior visits) scales and definitions will be used for overall tolerability evaluations (with half-point scores used as necessary to better describe the clinical condition):

Objective Irritation Parameters:

| Erythema | |
| --- | --- |

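### The between-arm tests at weeks 4 and 8 use no baseline covariate, so they are valid on average but less precise than an ANCOVA on the baseline grade already collected.

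*Protocol*

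**What the plan says.** The Statistical Analysis section of the protocol opens with the comparisons intended at weeks 4 and 8: "The clinical grading scores and tolerance scores (subjective and objective) will be compared for both treatments and with their respective baselines". It then separates two kinds of test.

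- **Within arm.** "For comparison with baseline of each treatment, the normality of the difference (from baseline) will be tested with Shapiro-Wilk test". A paired t-test or a Wilcoxon signed-ranks test follows. This is the only place where a difference from baseline is named as the analysed quantity.
- **Between arms.** "For comparing both the treatments with each other, the normality of the difference (between treatments) will be tested with Shapiro-Wilk test". The choice is then "Parametric t-test in case of normality of differences" or "Non-parametric Mann-Whitney test in the inverse case".

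The level for the comparisons is given as "For all other statistical tests, the statistical significance level is set at p≤0.05", without saying whether tests are one- or two-sided. The same section sets clinical significance at half a grade point or more, considered only once a result is statistically significant.

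Baseline grades exist for every subject. The Clinical grading assessments part of the protocol says: "Clinical grading of efficacy parameters will be performed at baseline, 4 & 8 weeks". There are seven face and four neck parameters, 11 in all. No covariate and no stratification of the randomization by baseline grade is stated anywhere. The Study endpoint section makes the contrast between the two arms the objective and describes it as a reduction in the study parameters.

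**The concern.** The trial's question is the between-arm difference, and the planned number of completers is small (42). Wrinkle, sagging and texture grades differ between people at entry, and a person's later grade can be expected to follow the earlier one to some extent. An unadjusted test of follow-up scores leaves all of that stable between-person spread in the error term. It also lets part of any chance difference in baseline means appear as a difference at weeks 4 and 8.

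Two things are at stake. One is the chance of detecting an effect as large as the protocol's own half-point threshold. The other is how the half-point rule is read, because an unadjusted difference in means can be moved towards or away from half a point by where the arms happened to start. The information that would reduce both problems is already collected.

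**Working it through.** **Is there a planning figure to reproduce?** No. The protocol gives 45 enrolled to complete 42 (a loss of 3/45 = 6.7%), with no power, SD or planning effect. What follows measures the consequence of the stated test.

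**Inputs from the protocol**
- 42 completers (Overview; Volunteer Selection).
- Allocation is not stated. The supplies list has 23 handles for 45 subjects, which suggests about 1:1, so 21 completers per arm is inferred.
- Difference of interest: 0.5 point (Statistical Analysis).
- Alpha 0.05, taken as two-sided.

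**Assumed inputs**
- SD of a grade: 0.75, 1.0 or 1.5 points, the same at baseline and follow-up.
- Baseline-to-follow-up correlation rho: 0.3 to 0.8.

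**Step 1: error variance relative to raw follow-up scores**
- Raw: 1. Change: 2(1 − rho). ANCOVA: 1 − rho².
- Raw against ANCOVA is 1/(1 − rho²). Change against ANCOVA is 2(1 − rho)/(1 − rho²) = 2/(1 + rho).

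| rho | Change | ANCOVA | Raw / ANCOVA | Change / ANCOVA |
| --- | --- | --- | --- | --- |
| 0.3 | 1.40 | 0.91 | 1.10 | 1.54 |
| 0.6 | 0.80 | 0.64 | 1.56 | 1.25 |
| 0.7 | 0.60 | 0.51 | 1.96 | 1.18 |
| 0.8 | 0.40 | 0.36 | 2.78 | 1.11 |

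The last two columns are roughly the factor by which the sample would have to grow to match ANCOVA. Below rho 0.5, change scores are noisier than raw scores.

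**Step 2: power for 0.5 point, 21 per arm, rho 0.7**
- Noncentrality = 0.5 / (s × √(2/21)), with √(2/21) = 0.309.
- s = SD for raw, SD × √0.60 for change, SD × √0.51 for ANCOVA.
- Noncentral t with 40 df (39 for ANCOVA).
- Example at SD 0.75: 0.5/0.231 = 2.16 (raw), 0.5/0.179 = 2.79 (change), 0.5/0.165 = 3.03 (ANCOVA).

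| SD | Raw | Change | ANCOVA |
| --- | --- | --- | --- |
| 0.75 | 56% | 78% | 84% |
| 1.0 | 35% | 53% | 60% |
| 1.5 | 18% | 28% | 31% |

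At SD 1.0, the results for raw, change and ANCOVA are 35.3/26.7/38.1% at rho 0.3 and 35.3/70.5/75.0% at rho 0.8.

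**Step 3: chance baseline imbalance**
- The SE of the baseline difference is SD × √(2/21) = 0.309 SD. The probability of a gap above 0.25 SD is 0.42.
- The probability of a gap of at least 0.5 point is 3% at SD 0.75, 11% at SD 1.0 and 28% at SD 1.5.
- On average a fraction rho of the gap carries into the unadjusted follow-up difference. At rho 0.7, a 0.5-point gap contributes 0.7 × 0.5 = 0.35 point.
- At SD 1.0 and rho 0.7, the false-positive rate given a 0.5-point gap is about 12%. Given a 0.25-point gap it is about 3%. Over all randomizations it averages to 5%.

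**The case against.** **The analysed variable is not named.** The between-arm sentence refers to a difference between treatments, which no single subject has in a parallel-arm trial. The Study endpoint section speaks of a reduction, which suggests change from baseline. A reader might infer that the plan discards the baseline grade altogether, but the documents do not establish that. Follow-up scores remain the plainer reading, because the section mentions a difference from baseline only for the within-arm tests. If changes were meant, baseline is used, though less efficiently than by ANCOVA.

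**The unadjusted test is not invalid.** This stands. Randomization keeps it unbiased, with a 5% error rate on average. A reader might also infer that a baseline gap passes in full into the week-8 result. Only a fraction rho does so on average. At SD 0.75 a gap of 0.25 SD is 0.19 point, of which about 0.13 carries over at rho 0.7.

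**SD and correlation are assumptions.** This also stands. The case with SD 0.75 and rho 0.7 taken alone would make ANCOVA look decisive, yet at SD 1.5 power stays near 31%. The entry floor of 4 for global wrinkles and facial sagging may narrow the baseline range and lower rho for those two grades, and at rho 0.3 the gain over raw scores is only 1.10 times. The protocol assigns grading to a blinded examiner role and does not say that one person grades throughout, so a high rho cannot be argued from that.

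**Could this be left to an analysis plan?** The protocol itself fixes the between-arm tests, so this is a stated choice.

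**Conclusion.** The point holds as one of efficiency. Under either reading of the protocol, the between-arm test is less precise than one adjusted for a baseline grade that is already collected for all 11 parameters. The direction does not depend on the assumed SD or on rho, apart from the one degree of freedom lost when rho is near zero. The size depends on both: slight against raw scores at rho 0.3, about a doubling of effective sample size at rho 0.7, and a smaller gain against change scores at rho 0.6 to 0.8.

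The documents do not support calling the planned test biased, or claiming that adjustment would make the trial adequately powered. The results rest on about 21 completers per arm, two-sided 0.05, equal SDs at baseline and follow-up, and the SD and rho ranges shown. The point concerns the clinical grades. For tolerance the gain is probably small, and baseline subjective tolerance records what subjects usually experience with similar products, which differs from what is recorded at later visits. The change should be made, but the planned analysis would not be wrong without it.

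**What to change.** In the Statistical Analysis section, for each clinical grading parameter:

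- Make the between-arm analysis at week 8, and likewise at week 4, an ANCOVA of the score on arm plus that parameter's baseline score.
- Assess normality on the model residuals, and use a rank-based ANCOVA in place of the Mann-Whitney test when normality is rejected.
- Report the adjusted mean difference with a 95% CI, and apply the half-point clinical-significance rule to that adjusted difference.

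Naming the score as the outcome and its baseline as the covariate also settles which variable is compared between arms. The tolerance scores may keep the planned tests.

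The cost is a change of analysis wording. It needs no new assessments, visits or subjects.

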**Volunteer Instructions**

**VOLUNTEER INSTRUCTIONS**

**Manual Group**

Pacific Bioscience Labs, Inc. would like to thank you for participating in this randomized, parallel arm home use test to evaluate signs associated with aging. You have been randomized to the manual application of the study facial cream group. The purpose of this evaluation is to assess the effectiveness in treating signs associated with aging of a prototype massage applicator in applying a facial cream compared to manual application of a facial cream over an 8 week period.

You will be given a study facial cream to use at home twice per day (morning and bedtime) for the next 8 weeks.

After using the facial cream for the first time and at each study visit you will complete an online questionnaire. In order to adequately complete the study questionnaires, please pay close attention to the following:

- Appearance of overall facial fine lines/wrinkles as well as the fine lines and wrinkles on the forehead, cheek, and upper lip/mouth
- Appearance of skin sagging on the face and neck areas
- Appearance of the lines between your eyes/eyebrows
- Overall appearance of the skin on your neck and neck folds
- Overall texture of the skin on your face and neck

For the next 8 weeks you will be asked to cleanse your face twice per day (approximately the same time each morning and evening prior to bedtime) using the cleanser and cleansing method you normally use. After cleansing, rinse your face with warm water, pat dry with a towel, and apply the study cream using the amount and technique you normally use when applying a facial cream. Please apply the study facial cream to your face and neck. Please do not change any other skin care routines except adding the study cream to your routine.

**Remember: You are asked to discontinue using your current facial moisturizer, serum and/or any other facial product, but please do not change cleaning method, skin care cleansing products for the study duration.**

You will be instructed to:

- Discontinue using your current facial moisturizer, serum, and/or any other facial skin care products
- Use the study facial cream twice per day (morning and bedtime) on your face and neck area
- Apply the study sunscreen to the face and neck (morning only). Please avoid contact of the sunscreen with the eyes. In the event the sunscreen comes in contact with the eye, rinse the eye with water to remove.

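### The between-arm test is chosen by a normality check on a between-treatment difference that no subject has in this parallel-arm trial

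*Protocol*

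**What the plan says.** The Statistical Analysis section of the protocol has two parallel paragraphs.

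- Within each arm, "the normality of the difference (from baseline) will be tested with Shapiro-Wilk test". The result decides between a paired t-test and the Wilcoxon signed-rank test.
- Between arms: "For comparing both the treatments with each other, the normality of the difference (between treatments) will be tested with Shapiro-Wilk test". The options are then "Parametric t-test in case of normality of differences" and "Non-parametric Mann-Whitney test in the inverse case".

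Normality is tested at 0.01 and everything else at 0.05. A difference of at least half a point counts as clinically significant, and is considered only once statistical significance is reached.

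On the design, the Overview table says "Subjects randomized to a treatment application method", and the Volunteer Instructions for both groups call the study a "randomized, parallel arm home use test to evaluate signs associated with aging". Under Clinical grading assessments, scores run from 0 to 9 and "half-point scores may be used as necessary to more accurately describe the skin condition". The Study endpoint section rests the trial's conclusion on the comparison of the two randomised groups.

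**The concern.** The between-arm paragraph repeats the structure of the within-arm one, but the quantity it needs is missing. A difference from baseline exists for every subject with both visits. A difference between treatments would need the same subject, or a matched pair, to have received both methods. The protocol describes no split-face, crossover or matched design. The tests that the gate selects, a t-test not called paired and a Mann-Whitney test, are for independent samples, so the gate does not fit them either.

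What is at stake is reproducibility of the analysis behind the study endpoint. Whoever runs it must invent a variable for the normality check. That choice can differ between analysts, and the resulting test can differ between parameters and visits. The rule governs 38 comparisons: 7 face + 4 neck = 11 grading parameters at 2 visits (22), plus 8 tolerance items at 2 visits (16).

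**Working it through.** The protocol gives no SD, power or sample-size derivation, so there is no figure of its own to reproduce. The check has three steps.

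**Inputs from the protocol.** 42 completers, hence 42/2 = 21 per arm if allocation is 1:1 (the ratio is not stated); half-point scores; gate at 0.01; comparisons at 0.05 (taken as two-sided, since sidedness is not stated). **Assumed:** the SD and shape of the change scores.

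**Step 1. Does the tested quantity exist?** For subject *i*, the change from baseline, Y_i(visit) − Y_i(baseline), is observed. The between-treatment difference, Y_i(applicator) − Y_i(manual), is not, because only one term is ever seen. The other literal meaning, the difference of the two arm means, is a single number per parameter and visit and has no sample distribution to test. Shapiro-Wilk therefore has no input under either meaning.

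**Step 2. Do sensible repairs agree on the test?** Two readings need no new design feature: (a) test the changes in each arm and use Mann-Whitney if either arm rejects; (b) test the pooled residuals, change minus own arm mean. Simulation with 21 per arm, normal changes rounded to 0.5 and 600 trials per SD gave these shares sent to Mann-Whitney:

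| Assumed SD | (a) either arm rejects | (b) pooled residuals reject | Gap (a − b) |
|---|---|---|---|
| 0.3 | 100% | 65% | 35 points |
| 0.4 | 94% | 45% | 49 points |
| 0.5 | 60% | 28% | 32 points |
| 0.6 | 32% | 15% | 17 points |
| 0.75 | 17% | 8% | 9 points |

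The gap is a lower bound on the share of trials in which the two readings pick different tests. The underlying changes were normal, so the rejections come mainly from half-point rounding. They fade as the SD grows: single-arm rejection was about 6% at SD 0.8 and 4–5% at SD 1.0.

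**Step 3. Does the significance verdict change?** It can change only when the t-test and Mann-Whitney disagree at 0.05 on the same data. A second simulation used 21 per arm, 400 trials per scenario, and a spread parameter of 0.5 or 0.75.

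- Normal changes: the tests disagreed in 1.3–1.5% of trials with no effect and 4.5–5.2% with a 0.5-point effect. These are ceilings on how often the choice between (a) and (b) could alter the verdict.
- Skewed or zero-inflated changes: the tests disagreed more often (3.3–5.0% with no effect, 9.5–33.5% with a 0.5-point effect). But (a) and (b) both chose Mann-Whitney in 99–100% of trials, so the two readings hardly diverge.
- Rejection rate with no effect under (b), over all shapes: 0.043–0.065. The simulation standard error is √(0.05 × 0.95/400) ≈ 0.011.
- A separate run gating on each arm's change (800 trials per cell) gave 0.045–0.061 with no effect, against 0.044–0.072 for the t-test alone and 0.044–0.061 for Mann-Whitney alone.

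**The case against.** The strongest defence is that the phrase is loose wording. Only the within-arm t-test is called paired, the between-arm tests are plainly for independent samples, and a statistician would check changes by arm or residuals without a second thought. A statistical analysis plan, not shown, may say so. Error rates look sound, and a normality gate, though weak, is a workable prespecified rule once its variable is named. Most of this stands and limits the size of the point. It does not remove it: the protocol states a rule on the wrong quantity, which differs from leaving a detail to a later document, and the natural repairs do not always choose the same test.

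Three stronger readings are tempting, and the documents do not support them.

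- *That the test depends on arbitrarily pairing unrelated subjects.* The protocol prescribes no pairing, and the selected tests use none. Even if an analyst paired subjects at random, the second simulation found that the verdict depended on the pairing in 0.7–3.3% of trials with no effect and 4–21% with a 0.5-point effect. Rejection with no effect was 0.045–0.070.
- *That the arms are unequal and so cannot be matched.* The supplies list has 23 applicators for 45 subjects, which suggests 45 − 23 = 22 manual subjects. But no ratio is stated, and 42 completers could be 21 and 21.
- *That a Mann-Whitney result cannot be held against the half-point rule.* The rule concerns a difference in grading scores, and the mean difference can be calculated whichever test supplied the p-value.

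**Conclusion.** The point holds in a limited form. The gate for the between-arm test is specified on a quantity that does not exist in this design, so a rule behind the study endpoint cannot be executed as written. Sensible readings can select different tests from the same half-point data. How often they do so depends on the SD, which the protocol does not give, and on approximate normality before rounding.

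The effect on conclusions is modest. Between the two sensible readings, the verdict could change in at most about 1.5% of comparisons with no effect and about 5% with a 0.5-point effect under normal changes, and rarely under the skewed shapes tried. No clear type I error inflation was seen. These figures assume 21 per arm, two-sided 0.05 and the simulated shapes. This should be corrected because the correction is cheap and the rule is wrong as written, but it does not by itself undermine the trial.

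**What to change.** In the Statistical Analysis section, delete the Shapiro-Wilk gate for between-arm comparisons and fix one analysis for every clinical grading parameter at weeks 4 and 8:

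score at visit = β0 + β1 × arm + β2 × baseline score + error

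Report β1, the baseline-adjusted mean difference between arms, with its 95% CI, and set it against the half-point threshold. Run Mann-Whitney on change from baseline as a sensitivity analysis in all cases, whatever the distribution looks like. The same gate also governs the tolerance scores, so name one fixed test for them too; Mann-Whitney is already in the plan.

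If the sponsor prefers to keep the gate, the minimum correction is to say what it is applied to: either the model residuals or the change from baseline within each arm, with a statement of what happens when only one arm rejects. The within-arm paragraph can stay, since its difference exists.

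The cost is about two sentences and slightly more analysis. Baseline scores are already collected, and no visit, assessment or sample size changes.

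### No primary endpoint or success rule is fixed among 22 between-arm grading tests at p≤0.05; if any one may count, chance alone favours the applicator in about 13–34% of trials

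*Protocol*

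**What the plan says.** Under Study Endpoints the protocol lists seven facial gradings ("Face: Forehead wrinkles, cheek wrinkles, lip area wrinkles, global facial wrinkles, facial sagging, glabella lines, texture") and four neck gradings ("Neck: Overall appearance, sagging, neck folds, texture"), with no order of importance.

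The only statement of success is under the heading Study endpoint: "There is a statistically/clinically significant reduction in the study parameters between the subjects randomized to the Anti-aging applicator with prototype cream", compared with manual application. It names no parameter and no visit.

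The Statistical Analysis section compares the arms on the grading and tolerance scores at both week 4 and week 8, using a t-test or a Mann-Whitney test. It sets one level throughout: "For all other statistical tests, the statistical significance level is set at p≤0.05". It does not state whether tests are one- or two-sided. It defines clinical significance as a grading difference of at least half a point and adds: "Clinical significance will be addressed only when the data is statistically significant".

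**The concern.** The purpose of the trial is to show that the applicator with cream does better than cream applied by hand. With many unranked comparisons at the full 5% level and no rule for combining them, the decision on which results amount to success can be made after they are seen. One favourable grading at one visit could then be presented as meeting the endpoint, and the protocol gives no ground for rejecting that reading.

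This is more than detail that an analysis plan could supply. The primary comparison and the success rule belong in the protocol. Here the protocol does state a rule, but it is one that two readers could apply to the same data and reach opposite conclusions.

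**Working it through.** **Plan's own figure.** The only design figure is 45 enrolled to complete 42. No power, effect size, standard deviation (SD) or overall error rate is given, so there is no calculation to reproduce.

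**Inputs from the protocol**
- Gradings: 7 face + 4 neck = 11.
- Post-baseline visits compared: 2, so 11 × 2 = 22 between-arm grading tests. The tolerance scores would add 8 × 2 = 16 and are left out here.
- Level: 0.05 per test.
- Completers: 42. The supply list has 23 applicators for 45 subjects, which points to roughly equal arms, so 21 per arm is assumed.

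**Assumptions not in the protocol**
- Two-sided tests.
- Correlation of 0.2–0.8 between gradings and 0.5–0.8 between visits.
- Normal data with a common SD, so that the t-test applies.

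**Upper reference: 22 independent tests, no true effect**
- Either direction: 1 − 0.95^22 = 0.676.
- Favouring the applicator (2.5% tail of each test): 1 − 0.975^22 = 0.427.

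**Correlated tests, by simulation** (at least 10,000 trials per setting, no true effect). Chance of at least one significant result:

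| Correlation between gradings | Correlation between visits | Either direction | Favours applicator |
|---|---|---|---|
| 0.2 | 0.5 | 62% | 34% |
| 0.2 | 0.8 | 56% | 31% |
| 0.5 | 0.5 | 50% | 26% |
| 0.5 | 0.8 | 44% | 23% |
| 0.8 | 0.5 | 32% | 16% |
| 0.8 | 0.8 | 27% | 13% |

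The lowest favourable figure lies between 13% and 14%, within simulation error. If only week 8 counted (11 tests), the ranges would be about 18–41% and 9–22%. If the tests were one-sided at 0.05, the favourable rate over 22 tests would be about 22–53%.

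**Half-point requirement.** With 21 per arm, the smallest significant t-test difference is t(0.975, 40) × √(2/21) = 2.021 × 0.3086 = 0.624 SD. This reaches half a point when the SD is 0.5 / 0.624 = 0.80. At or above that SD, essentially every significant t-test difference also clears half a point. Below it, the requirement removes some. Over the same correlations, the favourable false-positive rate with both conditions imposed is:

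| Assumed SD (points) | Favourable and at least 0.5 point |
|---|---|
| 0.5 | about 1% |
| 0.7 | 6–17% |
| 1.0 | 13–34% |

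**After a fix.** One named comparison has a 5% error (2.5% in favour of the applicator). Holm over two comparisons keeps the overall error at or below 5%.

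**The case against.** - **A reader might infer that any single significant parameter is the stated success rule.** The protocol does not say so. Its plural wording can also be read as requiring all parameters, and the error would then be below 5%. That stands, and it makes the rates above conditional. But nothing in the text selects that reading. It would also be hard to apply literally, because the Parameters row of the Overview includes photographs, tolerance and questionnaires.
- **A reader might take the 27–62% as the chance of a positive claim for a useless applicator.** It is not. It counts differences in either direction, whereas the endpoint calls for a reduction with the applicator. The relevant range is about 13–34% for two-sided tests, roughly half. Only one-sided testing at 0.05 would bring it to 22–53%, and sidedness is not stated.
- **A reader might take the slash in the endpoint to mean that either kind of significance is enough.** Clinical significance alone cannot be, because Statistical Analysis considers it only after statistical significance. What stays open is whether statistical significance without the half point counts as success.
- **The half-point criterion may protect well.** At an SD of 0.5 it does. So it would be wrong to say that the criterion gives little protection, and equally wrong to rely on it without an SD. The 0.62 SD threshold is also a t-test figure and does not carry over to the Mann-Whitney test.
- **A separate analysis plan may exist.** The choice of multiplicity procedure can reasonably be left to it, and its absence here is not the point. The missing primary comparison and success rule are.

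**Conclusion.** The point holds as a defect of definition with a conditional error rate. The protocol fixes neither a primary endpoint nor a success rule among 22 between-arm grading tests, each at 0.05. If any one may count, the chance of a false result in favour of the applicator is about 13–34%, against 2.5% for a single two-sided test, or about 5 to 14 times as high (13/2.5 = 5.2; 34/2.5 = 13.6). If the half point is also required, the rate runs from about 1% at an SD of 0.5 to 13–34% at an SD of 1.0.

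The count of tests, the common level and the missing rule come from the protocol. The correlations, the SDs, two-sidedness and 21 per arm are assumptions. The conclusion that the success rule is undefined depends on none of them. It should be settled before any superiority claim rests on this trial.

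**What to change.** - **Name the primary between-arm comparison at week 8.** Global facial wrinkles and facial sagging are a natural choice, since they are the only gradings with an entry threshold (at least 4). Test them two-sided with Holm at an overall 0.05. The documents do not dictate this pair; a different pre-specified choice, or a single grading, would also cure the defect.
- **Make the rest secondary.** Report the other nine gradings and all week-4 results as estimates with 95% confidence intervals and no superiority claim.
- **Reword the endpoint** to require a difference that is both statistically and clinically significant, with the half point applied to the between-arm mean difference. State the sidedness.

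**Cost.** The change is to wording only; no visit or assessment is added. Fewer parameters can support a claim. Holm's first step, at 0.025, raises the smallest significant difference from about 0.62 SD to t(0.9875, 40) × √(2/21) = 2.329 × 0.3086 = 0.72 SD, in a trial that states no power. A single primary grading would keep it at 0.62 SD, at the price of resting the claim on one parameter.
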